### Epigenetic age acceleration and pace of aging

Our study will employ eight representative epigenetic aging clocks to estimate epigenetic age acceleration and pace of aging: Horvath [38], Hannum [39], PhenoAge [40], GrimAge [41], DunedinPACE [42], GrimAge version 2 [43], PC-PhenoAge and PC-GrimAge [44].

The first-generation epigenetic clocks, the Horvath clock and the Hannum clock, are constructed solely based on DNA methylation data. Horvath [38] developed an epigenetic clock comprising 353 CpG sites by analyzing publicly available DNA methylation datasets from a wide range of human tissues and cell types. Hannum et al. [39] created an epigenetic clock based on 71 CpG sites, utilizing DNA methylation data from the blood of adults. Both the Horvath and Hannum clocks exhibit high accuracy in predicting chronological age.

The second-generation epigenetic clocks, such as GrimAge and PhenoAge, incorporate clinical biomarkers in addition to methylation data. The PhenoAge clock integrates 9 clinical blood biomarkers (albumin, alkaline phosphatase, creatinine, C-reactive protein, glucose, mean corpuscular volume, red cell distribution width, white blood cell count, and lymphocyte percentage) and 513 age-related CpGs [40]. The GrimAge clock [41] is composed of 7 DNA methylation-based plasma protein biomarkers, pack-years of smoking, and 1030 CpG sites. The plasma protein biomarkers include cystatin C, leptin, tissue inhibitor of metalloproteinase 1 (TIMP-1), adrenomedullin (ADM), beta-2-microglobulin (β2-M), growth differentiation factor 15 (GDF-15), and plasminogen activation inhibitor 1 (PAI-1) [41]. Both GrimAge and PhenoAge demonstrate strong correlations with lifestyle risk factors and perform well in predicting morbidity and mortality risks.

The third-generation epigenetic clocks, such as DunedinPACE [42], GrimAge version 2 [43], PC-PhenoAge and PC-GrimAge [44], are characterized by their integration of multi-dimensional data, optimization of algorithms and models, and ability to comprehensively assess individual health status, disease risk, and the effects of aging interventions. DunedinPACE [42] is developed based on longitudinal changes in multi-system biomarkers, reflecting the pace of aging, with its unit expressed as ‘years/calendar year’. GrimAge version 2 [43] expandes upon the original GrimAge by incorporating additional DNA methylation (DNAm)-based surrogates for clinically relevant plasma proteins (DNAm logCRP and DNAm logA1C). PC-PhenoAge and PC-GrimAge [44] are epigenetic clocks optimized based on principal component analysis (PCA). They utilize principal components derived from the CpG sites of the foundational PhenoAge and GrimAge clocks, offering high reliability and potential applications in personalized medicine, longitudinal tracking, *in vitro* studies, and clinical trials of aging interventions.

We have introduced a novel variable, ‘Mean EpiAge’ [45], which is calculated as the average methylation age derived from seven established epigenetic clocks: Horvath, Hannum, GrimAge, PhenoAge, GrimAge version 2, PC-PhenoAge, and PC-GrimAge. Notably, DunedinPACE is excluded from the computation of Mean EpiAge because it specifically quantifies the pace of aging rather than providing a methylation age estimate. The development of Mean EpiAge aims to reconcile discrepancies between DNA methylation age and chronological age that arise from the use of different epigenetic clocks, thereby offering a more comprehensive measure of biological aging. We will focus on the results of each epigenetic clock because they enable us to conduct comparisons with studies that utilize the same clocks. Similarly, we pay attention to the Mean EpiAge, as it represents an overall and comprehensive aging outcome.

Genomic DNA from blood samples will be extracted using the QIAamp 96 DNA QIAcube HT Kit and processed on the QIAcube HT automated nucleic acid extractor. Then we will employ the 935K DNA methylation array (Infinium Methylation EPIC BeadChip Kit) to assess the methylation status of the whole genome. To ensure data reliability, the methylation data will undergo comprehensive processing and quality control, which includes filtering out low-quality probes, normalizing the raw methylation data (converting it to β-values within the range of 0 to 1), and conducting batch effect analysis and correction. The online tool ‘DNA Methylation Age Calculator’ (https://dnamage.clockfoundation.org) developed by Horvath et al. [38] and open-source R packages will be used to calculate DNA methylation age. A file containing the methylation β-values for all samples and a file with brief annotation information need to be uploaded. After a period of online analysis, the platform will generate output files with the calculated DNA methylation age and other estimates.

### Frailty

This study will use the Fried phenotype [46] for frailty assessment, which includes weight loss, decreased gait speed, reduced handgrip strength, decreased physical activity, and fatigue. Individuals meeting three or more criteria will be classified as frailty, those meeting one or two criteria are classified as pre-frailty, and those meeting none of the criteria are classified as robust older adults. The frailty score ranges from 0 to 5.

### Intrinsic capacity

The assessment of IC will be conducted according to the five domains proposed by the World Health Organization (WHO), including cognitive, locomotor, vitality, psychological, and sensory domains [47]. We will employ the Mini-Mental State Examination (MMSE) [48], Short Physical Performance Battery (SPPB) [49], Mini Nutritional Assessment (MNA) [50], Geriatric Depression Scale-15 (GDS-15) [51], and self-reported vision and hearing status for the evaluations of five domains.

We consider the IC by integrating the values obtained from five domains. To obtain a summary score that represents IC, we calculated Z-score. A Z-score reflects the distance of an individual’s data point from the mean of the population we studied, measured in standard deviations. The interpretation of Z-score is as follows: a positive Z-score means that an individual’s raw score is higher than the population mean, while a negative Z-score indicates that the individual’s raw score is lower than the mean. In other words, the Z-score shows the number of standard deviations by which an individual’s raw score deviates from the population mean [52].

In previous studies focusing on IC, the IC Z-score is extensively employed as a robust and well-established measurement tool for assessing IC [53]. In this study, we first calculated the Z-score for each of the five domains. Then, we computed a composite IC Z-score. This composite score was calculated by taking the sum of the Z-scores of the five domains and dividing it by five. This method standardizes the five domains to the same scale before calculating the overall summary measure. The specific calculation steps are as follows:Single-domain Z-score: For each domain, the Z-score is calculated using the formula:

$$\text{Single}-\text{domain Z‐}\text{score}=\frac{\text{Individual}\prime \text{s measurement value }-\text{ Population mean value}}{\text{Population standard deviation}}$$
IC Z-score: The overall intrinsic capacity Z-score is obtained by averaging the Z-scores across the five domains:

$$\text{IC Z‐}\text{score}=\frac{\text{Sum of Z}-\text{scores across the five domains}}{5}$$

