**Figure 2. F0002:**
[figure not shown]
Flow chart of multidomain intervention.

The primary outcomes are the change in epigenetic age acceleration and pace of aging. We will apply eight representative aging clocks in our primary outcomes: Horvath, Hannum, GrimAge, PhenoAge, DunedinPACE, GrimAge version 2, PC-PhenoAge, and PC-GrimAge. Epigenetic age acceleration is defined as the residuals of the linear regression of DNA methylation age on chronological age, which can be calculated by seven clocks (Horvath, Hannum, GrimAge, PhenoAge, GrimAge version 2, PC-PhenoAge, and PC-GrimAge). The rate of aging represented by DunedinPACE is also the primary outcome we are concerned about.

The secondary outcomes are the changes in frailty score and IC Z-score. Other outcomes include physical functions, body composition, aging biomarkers, inflammatory markers, haematology and biochemistry parameters, and lifestyle factors (Table 1).

**Table 1. t0001:** Overview of outcomes and assessment time points.

Outcomes	Outcome measures	Screening	Baseline	6 months	12 months
Primary outcomes					
Epigenetic age acceleration and pace of aging	Horvath, Hannum, GrimAge, PhenoAge, DunedinPACE, GrimAge version 2, PC-PhenoAge, and PC-GrimAge		√	√	√
Secondary outcomes					
Frailty	Fried phenotype	√	√	√	√
Intrinsic capacity	IC Z-score: cognition: MMSE; locomotion: SPPB; vitality: MNA; psychology: GDS-15	√	√	√	√
Other outcomes					
Physical functions	Handgrip strength	√	√	√	√
	Gait speed: 4-m walk test	√	√	√	√
	Timed up-and-go test	√	√	√	√
	Five-times sit-to-stand test	√	√	√	√
Body composition	BMI, waist-to-hip ratio, skeletal muscle mass, skeletal muscle index, body fat percentage, visceral fat area, phase angle	√	√	√	√
Aging biomarkers	Telomere length		√	√	√
	Mitochondrial DNA copy number		√	√	√
Inflammatory markers	hsCRP, homocysteine		√	√	√
	IL-1β, IL-2, IL-4, IL-6, IL-8, IL-10, IL-13, IFN-γ, TNF-α, MCP-1, Eotaxin, CXCL9, CXCL10, CX3CL1, sTNF-R1, sTNF-R2, G-CSF、GM-CSF, VEGF, RANTES, TRAIL		√	√	√
Haematology and biochemistry parameters	Hemoglobin, platelets, neutrophils, hematocrit, white blood cell count; blood urea nitrogen, creatinine, uric acid, glucose, albumin, total bilirubin, alkaline phosphatase, alanine transaminase (ALT), aspartate transaminase (AST), lipid profile		√	√	√
Lifestyle factors	Dietary diversity	√	√	√	√
	Physical activity and sedentary time	√	√	√	√
	Health literacy	√	√	√	√

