### Questionnaires

All assessment questionnaires will be completed by trained professional investigators through face-to-face interviews with the participants. The questionnaires will include demographic information (name, gender, age, marital status, education level, etc.), lifestyle factors (drinking, smoking, dietary diversity, physical activity and sedentary time, health literacy, etc.), medical history (hypertension, diabetes, hyperlipidemia, coronary heart disease, stroke history, etc.), and the standardized scales in comprehensive geriatric assessment.

MMSE: It assesses cognitive function, including orientation, immediate and delayed memory, attention, calculation, naming, repetition, reading, writing, and copying abilities, with a total score ranging from 0 to 30 [48].

SPPB: It evaluates balance, gait speed, lower limb strength, and functional capacity, with a total score ranging from 0 to 12 [49].

MNA: It includes evaluations of body weight, dietary intake, overall nutritional status, and measurements of mid-upper arm circumference and calf circumference, with a total score ranging from 0 to 30 [50].

GDS-15: It assesses the psychological state of older adults over the past week, focusing on mood, interest, fatigue, and feelings of self-blame through 15 questions, with a total score ranging from 0 to 15 [51].

Vision and hearing: participants select the most appropriate response to describe their condition: ①normal (0 points); ② mild decline (1 point); ③ limited in daily life (2 points); or ④ severe decline (3 points). The sensory score was calculated as the sum of the vision and hearing scores.

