### Physical examinations

Handgrip strength: Handgrip strength will be measured using a electronic handheld dynamometer (Jamar, USA) while the participant is seated. Participants will apply force gradually until reaching the maximum value. Three measurements will be taken for each hand, and the highest value will be recorded [54].

Gait speed: Gait speed will be assessed by a 4-m walk test. Participants is instructed to walk a straight 4-m distance at a normal pace from the same starting point. The average time of the two trials will be taken as gait speed [55].

Timed up-and-go test: Participants will sit in a chair with armrest. After standing up, they will walk forward 3 meters at their normal walking speed. Upon crossing a marked line, they will turn around and walk back to the chair, then sit down again with their back against the chair’s backrest. The tester will record the time from when the participant’s back leaves the chair’s backrest until they are seated and leaning back against it again [56].

Five-times sit-to-stand test: Participants will sit in a chair without armrests with their hands crossed over their chest. Upon hearing the instruction, they will quickly complete five stands and sits. The tester will record the time from the start until the participant’s last sit-down [57].

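### The intrinsic capacity Z-score averages domains that run in opposite directions with no sign reversal, so better mood, vision or hearing lowers this secondary outcome

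*Protocol article*

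**What the plan says.** The section on intrinsic capacity gives an explicit recipe. Each domain Z is the individual value minus the population mean, divided by the population SD, and "a positive Z-score means that an individual’s raw score is higher than the population mean". The composite is then defined twice, once in the text, "This composite score was calculated by taking the sum of the Z-scores of the five domains and dividing it by five", and once with the equation: "The overall intrinsic capacity Z-score is obtained by averaging the Z-scores across the five domains". The text claims one kind of harmonisation: "This method standardizes the five domains to the same scale before calculating the overall summary measure". Direction is not mentioned.

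The Questionnaires section codes vision and hearing from 0 (normal) to 3 (severe decline) each, and adds: "The sensory score was calculated as the sum of the vision and hearing scores". GDS-15 is described as "focusing on mood, interest, fatigue, and feelings of self-blame through 15 questions, with a total score ranging from 0 to 15", with no statement of which end is favourable. MMSE, SPPB and MNA are given as scores out of 30, 12 and 30.

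Table 1 lists the components as "IC Z-score: cognition: MMSE; locomotion: SPPB; vitality: MNA; psychology: GDS-15", which is four, without the sensory domain. The Introduction presents IC as a positive state, in contrast to frailty as a negative one.

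**The concern.** A composite of Z-scores has a meaning only if every component points the same way. Here three components rise with better function. One (sensory) rises with worse function by the article's own coding. One (GDS-15) does so on the ordinary reading of a depression scale. Since the printed formula gives each a weight of +1/5, a participant who becomes less depressed, or who reports better hearing, gets a lower IC score.

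The outcome affected is one of only two secondary outcomes. A between-arm difference in it could be diluted, or in some patterns reversed. Even without dilution, a positive result could not be read as a gain in intrinsic capacity.

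**Working it through.** **Inputs from the article**

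- Weights: +1/5 for each of five domains (Intrinsic capacity).
- Sensory: vision plus hearing, each 0 to 3, so 0 to 6, higher = worse (Questionnaires; explicit).
- GDS-15: 0 to 15, higher = worse (inferred from its being a depression scale; not stated).
- MMSE: low scorers are excluded as impaired, so higher = better (Inclusion and exclusion criteria).
- SPPB and MNA: scores of function and nutritional status, read as higher = better.
- Domain effects, SDs and correlations for IC: none given. The sample size section covers epigenetic age acceleration and frailty only, so there is no stated IC figure to reproduce.

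**Share of benefit cancelled**

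Let A be the summed gain, in SD units, over MMSE, SPPB and MNA, and B the summed gain over GDS-15 and sensory, with a gain always meaning a change for the better.

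- Correctly signed composite: (A + B)/5
- As written: (A - B)/5
- Share cancelled: 1 - (A - B)/(A + B) = 2B/(A + B)

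The share reaches 50% when 4B = A + B, that is B = A/3. The composite changes sign once B exceeds A.

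With a gain of d in each of MMSE, SPPB and MNA (A = 3d):

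| Gain in GDS-15 | Gain in sensory | Correct | As written | Cancelled |
|---|---|---|---|---|
| d | d | 1.00d | 0.20d | 80% |
| d | 0 | 0.80d | 0.40d | 50% |
| 0.5d | 0.5d | 0.80d | 0.40d | 50% |
| 0.5d | 0 | 0.70d | 0.50d | 29% |
| 0.25d | 0 | 0.65d | 0.55d | 15% |
| 0 | 0 | 0.60d | 0.60d | 0% |

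If only GDS-15 gains d and nothing else moves, the correct change is +0.20d and the as-written change is -0.20d.

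If Table 1's four components governed instead, GDS-15 gains of d, 0.5d, 0.25d and 0 would cancel 50%, 29%, 15% and 0%.

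**Does power fall?**

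Assume a 0.30 SD gain per fully improved domain, a common correlation r = 0.3 between correctly signed domains, unit SDs and two-sided alpha 0.05. Take 99 evaluable per arm (124 x 0.80 = 99.2, using the article's 20% dropout). The composite SD is 0.663 correctly signed and 0.390 as written, because mixed signs partly cancel shared variance.

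| Domains that improve | Power, correct | Power, as written |
|---|---|---|
| All five equally | 89% | 19% |
| Four equally, sensory flat | 72% | 58% |
| Three trained, GDS-15 at half | 60% | 77% |
| Three trained, GDS-15 at a quarter | 54% | 84% |
| Three trained only | 48% | 90% |

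At 74 per arm and r = 0.2 the pattern is the same: 86% v 14% for five equal gains, and 45% v 76% for the three trained domains only.

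**Does the score still measure IC?**

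Under the same equal-correlation assumption, the as-written score correlates with the correctly signed one at 0.20 (r = 0), 0.29 (r = 0.2), 0.34 (r = 0.3) and 0.39 (r = 0.4).

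**The case against.** The best defence is that reversing adverse scales is a routine scoring step which an article may leave out, and that the article cites an established IC Z-score method. The analysts may well do it. But the article does not leave the scoring open. It prints the equations, says what a positive Z means in terms of the raw score, and gives the sensory coding. If reversal is intended, the printed formula is still wrong.

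The second objection concerns size, and it stands. A reader might infer that half or more of a real benefit is lost in general. The documents do not support that. The intervention consists of cognitive training, exercise and nutritional guidance, which correspond to the three correctly signed domains, and it has no vision, hearing or mood component. A loss of 50% or more needs B to be at least A/3, and the 80% case needs self-rated vision and hearing to improve as much as the trained domains.

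A reader might also infer a collapse in power, such as 89% to 19%. That is one scenario; if only the trained domains respond, the as-written score has the higher power. The calculation also uses cross-sectional SDs, although the outcome is a change.

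Finally, the direction of GDS-15 is inferred; only that of the sensory score is stated. Even if GDS-15 were set aside, one of five components would still carry the wrong sign.

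**Conclusion.** The formula is wrong as written. Applied literally, it gives a secondary outcome in which one component certainly, and a second on the ordinary reading of the scale, enters with the wrong sign. The firm harm is to validity: the composite does not measure intrinsic capacity, whatever the treatment effect.

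The dilution runs from 0% to 80% if the three trained domains gain equally and mood and sensory function gain no more than they do. The sign reverses if only mood or sensory function improves. These are scenarios, since the article gives no domain effects. The direction of the power effect is not determined.

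The conflict between four components in Table 1 and five in the text is a separate defect in the definition of the same outcome. The primary epigenetic outcomes are unaffected.

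**What to change.** In the section on intrinsic capacity, state that the Z-scores of GDS-15 and of the sensory score are multiplied by -1 before averaging, so that higher means better in every domain. State the direction of GDS-15 in the Questionnaires section. Reconcile the IC row of Table 1 with the five-domain formula, since a four-component and a five-component score are different outcomes. This takes a few sentences and one table cell, needs no new data, and should be settled before the analysis.

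A separate minor point, which has no bearing on the argument above: under Physical examinations, "The average time of the two trials will be taken as gait speed", although a longer time means slower walking. Define gait speed as 4 m divided by the mean time.

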### Questionnaires

All assessment questionnaires will be completed by trained professional investigators through face-to-face interviews with the participants. The questionnaires will include demographic information (name, gender, age, marital status, education level, etc.), lifestyle factors (drinking, smoking, dietary diversity, physical activity and sedentary time, health literacy, etc.), medical history (hypertension, diabetes, hyperlipidemia, coronary heart disease, stroke history, etc.), and the standardized scales in comprehensive geriatric assessment.

MMSE: It assesses cognitive function, including orientation, immediate and delayed memory, attention, calculation, naming, repetition, reading, writing, and copying abilities, with a total score ranging from 0 to 30 [48].

SPPB: It evaluates balance, gait speed, lower limb strength, and functional capacity, with a total score ranging from 0 to 12 [49].

MNA: It includes evaluations of body weight, dietary intake, overall nutritional status, and measurements of mid-upper arm circumference and calf circumference, with a total score ranging from 0 to 30 [50].

GDS-15: It assesses the psychological state of older adults over the past week, focusing on mood, interest, fatigue, and feelings of self-blame through 15 questions, with a total score ranging from 0 to 15 [51].

Vision and hearing: participants select the most appropriate response to describe their condition: ①normal (0 points); ② mild decline (1 point); ③ limited in daily life (2 points); or ④ severe decline (3 points). The sensory score was calculated as the sum of the vision and hearing scores.

### Physical examinations

Handgrip strength: Handgrip strength will be measured using a electronic handheld dynamometer (Jamar, USA) while the participant is seated. Participants will apply force gradually until reaching the maximum value. Three measurements will be taken for each hand, and the highest value will be recorded [54].

Gait speed: Gait speed will be assessed by a 4-m walk test. Participants is instructed to walk a straight 4-m distance at a normal pace from the same starting point. The average time of the two trials will be taken as gait speed [55].

Timed up-and-go test: Participants will sit in a chair with armrest. After standing up, they will walk forward 3 meters at their normal walking speed. Upon crossing a marked line, they will turn around and walk back to the chair, then sit down again with their back against the chair’s backrest. The tester will record the time from when the participant’s back leaves the chair’s backrest until they are seated and leaning back against it again [56].

Five-times sit-to-stand test: Participants will sit in a chair without armrests with their hands crossed over their chest. Upon hearing the instruction, they will quickly complete five stands and sits. The tester will record the time from the start until the participant’s last sit-down [57].

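### Gait speed, an 'other' outcome, is defined as an average walking time, so its unit and direction are wrong as written; the Fried slowness item may be affected, but the article does not say

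*Protocol article*

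**What the plan says.** Under Physical examinations, participants are asked to "walk a straight 4-m distance at a normal pace from the same starting point". The derivation follows: "The average time of the two trials will be taken as gait speed". Neither a division of distance by time nor a unit is given.

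Table 1 lists the variable as "Gait speed: 4-m walk test", under physical functions within the other outcomes, measured at screening, baseline, 6 months and 12 months.

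Gait speed also appears by name in two other instruments:

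- **Frailty section:** the Fried phenotype is adopted, "which includes weight loss, decreased gait speed, reduced handgrip strength, decreased physical activity, and fatigue", and "The frailty score ranges from 0 to 5". No cut-off or unit is given for the gait item, and the section does not refer to the 4-m walk.
- **Questionnaires section:** of the SPPB it is said that "It evaluates balance, gait speed, lower limb strength, and functional capacity". No separate walking procedure is described there.

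On the outcome hierarchy, "The secondary outcomes are the changes in frailty score and IC Z-score".

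**The concern.** The article gives an explicit rule for deriving a listed outcome, and the rule equates a time with a speed. It is therefore not a detail left to a fuller document. Nor is it a general convention of the section: the timed up-and-go and the five-times sit-to-stand are also recorded as times, but neither is called a speed.

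Followed literally, the rule enters a participant who walks faster with a lower gait speed, so a benefit would read as a decline. A value in seconds also cannot be set beside results reported in m/s.

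A second question is whether the same value is used to score slowness in the frailty assessment. One point of a five-point secondary outcome depends on that item, so it matters that the criterion and the recorded value run in the same direction.

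**Working it through.** The plan gives no gait data and no figure to reproduce. The check is one of dimension and direction, with illustrative times.

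**Inputs**
- Distance: 4 m, fixed (Physical examinations).
- Recorded value: mean time of two trials (same section).
- Unit of time: seconds. This is an assumption, because the text says only time.
- Trial times of 3 to 5.5 s: illustrative assumptions.

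**Formulas**
- As written: gait speed = mean time (s).
- By definition: gait speed = 4 m / mean time (m/s).

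**Results**

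| Mean time (s) | Recorded as gait speed | 4 / mean time (m/s) |
|---|---|---|
| 3.0 | 3.0 | 1.333 |
| 4.0 | 4.0 | 1.000 |
| 5.0 | 5.0 | 0.800 |
| 5.5 | 5.5 | 0.727 |

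The recorded value rises as true speed falls, so the direction is reversed throughout.

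**One participant improving from 5.0 s to 4.0 s**
- True speed: 4/5.0 = 0.80 m/s to 4/4.0 = 1.00 m/s; change (1.00 - 0.80)/0.80 = +25%.
- Recorded value: 5.0 to 4.0; change (4.0 - 5.0)/5.0 = -20%.

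**Would reversing the sign at the end be enough?** No, because speed is the reciprocal of time. Take two participants at 4.0 s and 5.0 s. Their mean speed is (1.000 + 0.800)/2 = 0.900 m/s. Converting their mean time instead gives 4/4.5 = 0.889 m/s. The conversion should therefore be made for each participant before group summaries are formed.

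**Does it matter how the two trials are combined?** Hardly.
- Trials of 3.6 s and 4.4 s: 4/mean time = 1.000 m/s; mean of the two speeds = 1.010 m/s.
- Trials of 4.5 s and 5.5 s: 0.800 against 0.808 m/s.

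The difference is about 0.01 m/s, so either rule would serve if stated.

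**Link to frailty.** Set side by side, the Physical examinations section does not mention frailty, and the Frailty section names a gait item without a source measurement, unit or cut-off. The 4-m walk is the only procedure described that could supply the item. That makes its use a reasonable inference, but the text does not establish it.

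**The case against.** The strongest reply is that this is compressed wording. The paragraph opens by saying that gait speed is assessed, states the distance and cites a method source. The sentence at issue may only have been meant to say that two trials are averaged. Because the distance is fixed, time converts exactly to speed and no information is lost. The +25% and -20% above are one improvement on two scales, not a bias. A value of 4 or 5 for a 4-m walk would also strike most readers as a time. Finally, the repeated-measures analyses in the Statistical analysis section are specified for primary and secondary outcomes, so no named test is tied to gait speed.

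All of this stands, and it keeps the point minor. It does not make the sentence correct: no other part of the article supplies the division or the unit.

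A reader might go further and infer that the frailty score is corrupted, with the slowness item lost so that the score effectively runs from 0 to 4, or with the item inverted. The documents do not support that. The item would be lost only if values in seconds were compared with a cut-off in m/s, and the article gives no cut-off. Inversion would require a lower recorded time to be scored as slower. If the item is scored from walking time with longer meaning slower, nothing goes wrong at all. The article does not say which of these applies, and it gives the frailty score range as 0 to 5.

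**Conclusion.** The definition is wrong as written: gait speed is recorded as a time, with the wrong dimension and a reversed direction. This conclusion needs no assumption beyond the fixed 4-m distance. The numerical examples also assume seconds and illustrative walking times.

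The variable directly affected is one of the other outcomes. No primary outcome, sample size or power figure changes. An effect on the Fried slowness item, and so on a secondary outcome, is possible because no other gait-speed procedure is described, but it is not shown. Its size cannot be calculated from the article. Minor severity.

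**What to change.** - Replace the sentence with a definition: gait speed is 4 m divided by the mean time of the two trials, in m/s, calculated for each participant at each visit. Use that value for the gait-speed outcome in Table 1.
- If the time is also kept, give it its own label, such as 4-m walk time (s), lower is better.
- In the Frailty section, state which measurement scores the slowness item, and make sure that its unit and direction match the criterion applied.

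The cost is one corrected sentence and one clarifying sentence. The times are already recorded, so neither new data nor extra visits are needed, and values already entered can be converted exactly.
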